### Interventions

#### Supplements

Eligible participants will be asked to maintain their usual dietary intake and current exercise habits, abstain from using any pain medication, and sports supplements that are not provided during the course of the study. The intervention groups will be provided capsules of PEA (350 mg/day as 2 × 175 mg Levagen + ® capsules), or identical matching placebo capsules (in colour and weight) containing maltodextrin (2 × 175 mg capsules), which will be taken orally (swallowed) for 8-weeks. On training days, participants will be instructed to take 1 × capsule 45 - 60 min prior to exercise with their standardised meal (388 kcals, 45 g CHO, 21 g PRO, 13 g FAT) and 1 × capsule in the evening 60 min prior to sleep [32]. The supplement taken prior to exercise is provided based on the time to peak blood concentrations of PEA (~ 45–60 min) [34]. On non-training days, participants will be asked to consume 1 × capsule with their morning meal and 1 × capsule pre-sleep, 60-min prior as per training days. The dosage of the supplement within this study is well below previous studies that have shown dosages of up to 1,200 mg/day have no harmful effects [35]. In the rare case that a participant may experience undesirable side effects, the blind will be broken, and participants will be referred to a local general practitioner and they may withdraw from the study.

The trial products will be supplied by Gencor Pacific (Lantau Island, Hong Kong) and manufactured by Pharmako Biotechnologies (Sydney, Australia). Compliance with dosing at home will be assessed by pill count and a tracker sheet at the end of the study.

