#### Muscle strength and power

Prior to any exercise testing participants will be provided with a standardised breakfast (388 kcals, 45 g CHO, 21 g PRO, 13 g FAT).

A force plate (400 s + Performance Force Plate, Fitness Technology, Adelaide, Australia) will be used to assess lower body strength and power during isometric mid-thigh pull (IMTP) and countermovement jump (CMJ) tests, respectively. The force plate will be interfaced with computer software (Ballistic Measurement System; Fitness Technology, Adelaide, Australia). The CMJ outcomes will be jump height (cm), peak force (N), peak power (W). The outcomes for the IMTP will be peak force (N) and peak power (W). Participants will undergo a standardised warm-up prior to performing 3 maximum-effort attempts of the CMJ and IMTP, respectively. The highest value of the 3-maximium efforts for the exercise will be analysed and reported to compare group differences.

Upper body power will be assessed using a bench throw performed using a Smith machine squat rack (Maxrack, IP-L8505, Star trac, Irvine, California, United States). A linear position transducer (GymAware v2.4.1, GymAware, Kinetic Performance Technology, Canberra, Australia) will be attached to the Smith machine barbell and used to assess barbell velocity (m/s) and power (W). Following a standardised warm-up, participants will perform 3 sets of 4 repetitions with a 2-min rest interval between sets. The highest value for the 3-maximum attempts for peak velocity (m/s) and peak power (W) will be recorded for each participant.

Lastly, upper body strength will be assessed by a 1-repetition maximum (1-RM, kg) bench press using a free weight bench press. Participants will first perform a warm-up involving 8, 5, and 3 repetitions with 50%, 75%, and 95% of predicted 1-RM, respectively. Participants then will perform 1-RM attempts with increasing loads (5–10 kg for males; 2.5–5 kg for females), with a 2.5 kg minimum load, until the 1-RM is reached. Participants will rest for 3 min in-between sets [38].

For all strength and power performance outcomes, the mean group difference at pre-testing vs post-testing will be reported.

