#### Self-reported questionnaires

Questionnaire data will be collected using Research Electronic Data Capture (REDCap) via participants own phones using a QR code. All questionnaire data will be recorded at familiarisation (week 0) and in weeks 2, 5 and 9. Outcomes measured in the self-reported questionnaire includes measurements or pain, menstrual pain, overall wellbeing, and sleep all of which are detailed below:To measure perception of pain associated with DOMs, participants will be asked to ‘rank their current level of pain’ using a 10-point visual analogue scale.Only female participants will be required to fill in a premenstrual symptoms screening tool (PSST) [39]. Alongside the questionnaire female participants will also be asked to track their menstrual cycle during the study on an electronic calendar and will be asked to mark the days of their menstruation 1-month prior to commencing the trial as well as during. For females that are on or taking hormonal contraceptive methods, the type of contraceptive will be recorded.To measure subjective wellbeing, the Short Recovery and Stress Scale (SRSS) questionnaire will be used to monitor wellbeing [40].Sleep quality will be assessed using the Pittsburgh Sleep Quality Index (PSQI) [41].

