### Allocation concealment and blinding

The supplement and placebo are provided by Gencor Pacific Ltd and will be provided in white opaque identical containers labelled either ‘A’ or ‘B’. The contents of each container will be provided in a sealed envelope that will only be made available to the researcher responsible for the sequence allocation who is not associated with the study. The researchers responsible for data collection and participant management will both be blinded to the groups and will not be made aware of the group allocation until after the data analysis.

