### Methods: data collection, management and, analysis

#### Data management and monitoring

Research assistants that are blinded to the supplement allocation will be trained on how to collect data. Data for body composition and exercise testing will be collected at the same location throughout the study. These data will be collected electronically, and research assistants will also backup electronic data using de-identified, participant coded data collection sheets. The electronic data is stored on password protected computers and the data sheets are stored in a locked filing cabinet. All research data collected will be transferred to an excel worksheet on password protected servers. While data is being collected, all data will be checked for omissions or errors by the project manager who will maintain a data diary of any issues that arise with the data. The data then will be checked again by the principal investigator (PI) and statistician prior to any analysis. The information collected from this study will be kept until the end of the project and then placed in archives for a minimum of 5 years from the final publication of the findings.

The CMJ, IMTP and bench throw will be taken in triplicate. A fourth measure may be taken if two of the measurements are not within ~ 10% of each other. Participants will have regular contact (2xdays/week) with the researchers and receive check-ins if they have missed sessions. Participants will have the opportunity to re-schedule missed sessions during the same week of training.

Any adverse effects recorded by participants will be reported directly to the PI. The PI will directly report adverse effects to the Therapeutic Goods Administration (TGA) in the Department of Health and Age Care, Australia. In the unlikely event of severe adverse reactions, the PI will make the final decision to terminate the trial.

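### Breaking the blind is automatic for any side effect, and the protocol does not say who is told or how this fits with keeping study staff blind

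*Protocol article*

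**What the plan says.** Three sections of the protocol article bear on this point.

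- **Supplements** (under Interventions) gives the trigger: "In the rare case that a participant may experience undesirable side effects, the blind will be broken". It continues that "participants will be referred to a local general practitioner and they may withdraw from the study".
- **Allocation concealment and blinding** says that the researchers who collect data and manage participants "will not be made aware of the group allocation until after the data analysis". The sealed key to the containers will "only be made available to the researcher responsible for the sequence allocation who is not associated with the study".
- **Data management and monitoring** has adverse effects reported to the PI and names a higher grade of event for a different decision: "In the unlikely event of severe adverse reactions, the PI will make the final decision to terminate the trial".

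On outcomes, Muscle strength and power has participants "performing 3 maximum-effort attempts of the CMJ and IMTP, respectively", and adds a bench throw and a 1-RM bench press. Self-reported questionnaires collects "measurements or pain, menstrual pain, overall wellbeing, and sleep". All of these are secondary. The primary outcomes are lean mass by DXA and mid-thigh area by pQCT.

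**The concern.** The trigger is mandatory and broad. Nothing restricts it to events of a given severity, or to cases where someone must know the allocation in order to act. The word rare says how often the authors expect such events; it does not say which ones count. Followed as written, the rule breaks the code in cases where the allocation is of no use to anyone.

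The person concerned need not leave the trial. A participant who learns the allocation can go on training, fill in the remaining questionnaires and take the final strength and power tests. If the allocation also reaches a trainer or assessor, encouragement and test conduct may change. If side effects are more frequent in one arm, so is the unblinding, and the resulting bias would not cancel between arms.

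**Working it through.** The trigger and the blinding rule are a matter of text, so the sections are set side by side first. The arithmetic after that is illustrative only.

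**1. What triggers a break.** Supplements: undesirable side effects, with a code break that will follow. No grade, no test of need and no decision-maker is stated. Data management and monitoring shows that the authors do distinguish severe reactions, but they attach that grade only to ending the trial. It does not narrow the trigger in Supplements.

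**2. Who learns the allocation.** Supplements does not say whether it is the participant, the general practitioner or the study team. Allocation concealment and blinding bars the data-collection and participant-management researchers from knowing and allows no exception.

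- If only the general practitioner or the participant is told, by the code holder outside the study, both rules can be kept.
- If anyone in the data-collection or management team is told, the blinding rule is broken.

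The text does not choose between these. Side effects reach the study team first, since adverse effects go to the PI, so the second case is a practical risk.

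**3. What happens next.** Withdrawal is permitted, not required. Questionnaires fall at weeks 0, 2, 5 and 9 and final testing at week 11, so outcomes can be measured after a break.

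**4. Which outcomes are exposed.**

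- *Directly, if the participant or an assessor knows:* jump, isometric pull, bench throw and 1-RM, which need maximal effort; and pain, wellbeing and sleep quality, which are self-reported. All are secondary.
- *Indirectly:* the DXA and pQCT measures. These are neither effort tests nor self-report, but the training behind them includes AMRAP sets from week 3, capsules are taken at home, and an unblinded participant may leave. Statistical methods describes the primary analysis as covering those who completed the trial, while also planning multiple imputation, so dropout after a break is relevant.

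**5. How many breaks.** The protocol gives no side-effect rate. The recruitment target is 52 (Sample size): 42 / (1 − 0.20) = 52.5, which agrees with the stated target and its approximate 20% dropout. For an assumed rate *p* per participant:

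expected breaks = 52 × *p*; chance of at least one = 1 − (1 − *p*)^52

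| Assumed *p* | Expected breaks | Chance of at least one |
|---|---|---|
| 1% | 0.52 | 41% |
| 2% | 1.04 | 65% |
| 5% | 2.6 | 93% |
| 10% | 5.2 | above 99% |

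These rates are assumptions. The table shows only that even a low rate makes at least one break plausible.

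**The case against.** The strongest reply is that the rule is narrower than it looks. The sentence speaks of a rare case and ties the code break to a medical referral and possible withdrawal, so the authors may have meant events that need medical attention. The term side effect also implies some suspected link to the capsules. That may be what was intended, but the sentence does not say it, and a site would follow the sentence. This part of the criticism stands.

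A second reply is that an article leaves unblinding procedures to the full protocol, which is not shown. That is fair for the mechanics, such as forms and logging, and their absence is not held against the plan here. The trigger is different: the article states it, and states it too broadly.

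Three stronger readings are tempting but are not supported.

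- *A reader might infer that the two blinding rules cannot both be followed.* They can, if the outside code holder tells only the general practitioner or the participant. What is missing is a statement that disclosure is confined in this way.
- *A reader might infer that the trial result as a whole is compromised,* especially since containers carry only two labels. The directly exposed outcomes are secondary, the primary ones are imaging measures, and the document does not say that a break reaches anyone who knows other participants' labels.
- *A reader might infer that later events would be judged for relatedness with the allocation known.* No section describes a relatedness assessment.

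**Conclusion.** The point holds in a limited form. As written, any side effect leads to a code break, with no test of need and no stated recipient, and the participant may stay in the trial. The rule that staff remain blind carries no exception, so the sections are compatible only under a restriction that neither states.

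Bias in the secondary effort-dependent and self-reported outcomes is a likely consequence if the participant or study staff are told; it is not something the text says will happen. The effect on the primary outcomes is indirect. The size is unknown because no side-effect rate is given; about 0.5 to 5 breaks among 52 participants rests wholly on the assumed 1% to 10%. This is an avoidable risk that is cheap to remove, and it should be corrected, but it is not a defect that by itself undermines the primary comparison.

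**What to change.** Reconcile Supplements, Allocation concealment and blinding, and Data management and monitoring so that they state one rule on code breaks:

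- The break is not automatic for every side effect. It is made only when knowledge of the allocation is needed.
- The independent researcher who already holds the key makes it, and discloses the allocation only to the person who needs it.
- Assessors, trainers and, where possible, the participant stay blind.
- Each break is recorded, and the participant stays in outcome follow-up.

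Referral and all other clinical handling of side effects are left to the sponsor; nothing here proposes a change to them.

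The cost is a few sentences in an amendment and no new staff, because the code holder exists. Trial status reports recruitment as still open, so at that stage the change could still protect participants not yet tested. The downside is that a participant with a minor complaint is not told the allocation during the trial.

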#### Resistance training

Participants will complete 8-weeks of supervised progressive resistance training twice per week on non-consecutive days at Deakin University Burwood campus. The sessions will be supervised by a qualified exercise trainer (e.g., exercise physiologist or qualified strength and conditioning coach) to monitor correct lifting and rest intervals. Each resistance training session (45 to 60 min in duration) will consist of eight exercises completed as four complex pairs. The exercises and complex pairs include: 1A leg press + 1B countermovement jump, 2A bench press + 2B bench press throw, 3A deadlift + 3B deadlift jumps, and 4A bench pull + 4B power bench pull. The strength-focused exercises (denoted with letter “A” of each complex pair) will be performed with a slow and controlled eccentric phase of ~ 2–3 s for increasing time under tension (stimulus for hypertrophy) and an explosive concentric phase (stimulus for strength and power development) with higher loads. The power-focused exercises (denoted with letter “B” of each complex pair) will be performed explosively (I.e., as fast as possible) in the eccentric and concentric phases with lower loads. The loads prescribed for the strength- and power-focused exercises will be calculated as percentages of the 1-RM either assessed directly (bench press) or predicted from a 6-RM (leg press, bench pull and deadlift) as determined in the familiarisation week**.** During weeks 3–8, an extra set will be performed for each of the strength-focused exercises whereby the load will be decreased (to 50 - 60% 1-RM) and participants will perform as many reps as possible (AMRAP). Some additional accessory exercises (e.g., leg curls, biceps curls and triceps pushdowns) to achieve muscle balance will also be added at this time. Rest between sets and exercises will range from 3–5 min. The prescription of the repetitions, sets and loads are outlined in Table 1.

**Table 1 Tab1:** Repetition, sets and loads to be used during the 8-week progressive resistance training program

	**Sets**	**Repetitions**	**Load** **(Strength exercises)**	**Load** **(Power exercises)**
Weeks 1–2	3	6	75% 1RM	45% 1RM
Weeks 3–4	3	5 AMRAP	80% 1RM 50-60%	50% 1RM
Weeks 5–6	4	4 AMRAP	85% 1RM 50-60%	55% 1RM
Weeks 7–8	5	3 AMRAP	90% 1RM 50-60%	60% 1RM

*AMRAP* as many reps as possible

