#### Statistical methods

A primary analysis of intention to treat (ITT) will be conducted of all the participants that have completed the trial. A secondary, per-protocol analysis will be carried out to include only participants that attend ≥ 80% of their resistance training and consumed ≥ 80% of their supplement over the course of the study. Between-group comparisons will be made using linear models adjusting for baseline outcome level and stratification factors sex and SMI (low/high). Outcome variables will be log-transformed where necessary to satisfy parametric assumptions. All tests will be two-tailed with statistical significance set at p < 0.05. Multiple imputation by chained equations will be used to handle missing data.

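### Home capsule intake is assessed only at the end of the study, although staff see participants twice a week, so low intake is found too late to correct

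*Protocol article*

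**What the plan says.** The Supplements section sets the intake at "350 mg/day as 2 × 175 mg Levagen + ® capsules", or matching placebo, "which will be taken orally (swallowed) for 8-weeks". On training days one capsule is tied to the session: participants are to "take 1 × capsule 45 - 60 min prior to exercise with their standardised meal". The other capsule that day, and both capsules on other days, are taken away from training. Adherence has one stated time point and two instruments: "Compliance with dosing at home will be assessed by pill count and a tracker sheet at the end of the study".

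The Resistance training section provides for "supervised progressive resistance training twice per week on non-consecutive days". Data management and monitoring adds: "Participants will have regular contact (2xdays/week) with the researchers and receive check-ins if they have missed sessions". Missed sessions can be rescheduled within the same week. The article describes no equivalent follow-up for missed capsules.

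Under Statistical methods, the secondary per-protocol set requires at least 80% training attendance and that participants "consumed ≥ 80% of their supplement over the course of the study".

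**The concern.** The capsules are what is randomised; both arms do the same training. Yet training attendance is followed while it can still be put right, and capsule intake is assessed once dosing is over. Two things are lost.

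- A participant who is missing capsules in the early weeks gets no prompt, so the loss continues to the end and weakens the contrast between arms in the primary analysis.
- If the returned capsules and the tracker disagree, the question is first asked up to 8 weeks after the event, when the participant may not remember.

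This is a choice the article states, not a detail it leaves out, and the contact needed to do better is already in the design.

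**Working it through.** **1. How much intake is out of sight of staff.** Inputs: 2 capsules a day for 8 weeks (Supplements); 2 sessions a week (Resistance training).

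- Full course: 8 × 7 × 2 = 112 capsules.
- Capsules tied to a session: 2 × 8 = 16, or 16/112 = 14%. The article does not say whether staff watch this capsule being taken, so 16 is an upper limit on what is observed.
- Taken away from sessions: at least 112 − 16 = 96, or 86%.

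**2. What the 80% rule tolerates.** 0.80 × 112 = 89.6, so 90 capsules are needed. A participant may miss 112 − 90 = 22 capsules, equal to 11 full days, and still count as per-protocol. The total can be worked out at the end as capsules dispensed minus capsules returned, with the tracker alongside. The rule is therefore workable as written. What it lacks is an earlier count against which unreturned or discarded capsules, or a tracker filled in late, could be checked.

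**3. The plan's own sample size.** Inputs (Sample size section): difference 2%, SD 2.2%, α = 0.05, 80% power, 21 per group. Statistical methods makes all tests two-tailed. For a two-sample t-test with n per arm, the noncentrality is d / (SD × √(2/n)) on 2n − 2 degrees of freedom.

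- n = 20: power 79.997%, just short of 80%.
- n = 21: standard error 2.2 × √(2/21) = 0.679; noncentrality 2/0.679 = 2.95; 40 df; power 82.0%.

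The stated 21 per group is reproduced.

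**4. Illustration of dilution.** Assumption, not in the article: the true difference equals 2% multiplied by mean intake in the PEA arm. With 21 per arm and SD 2.2%:

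| Mean intake | Difference | Noncentrality | Power |
|---|---|---|---|
| 100% | 2.0% | 2.95 | 82.0% |
| 90% | 1.8% | 2.65 | 73.5% |
| 80% | 1.6% | 2.36 | 63.3% |
| 70% | 1.4% | 2.06 | 52.1% |

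Under this assumption, mean intake of 90% costs 82.0 − 73.5 = 8.5 points of power, and 80% costs 82.0 − 63.3 = 18.7 points. The article gives no expected intake, so the table shows how sensitive the design would be, not what will happen.

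**The case against.** The strongest reply is that nothing here is wrong or contradictory. How often staff look at capsules is operational detail that an article may leave to the full protocol, and staff may well ask about capsules informally at the twice-weekly contacts. This stands as a limit on severity. It does not remove the point, because the article does state when home dosing is assessed, and that time is the end of the study.

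Three stronger readings are tempting, and the article does not support them.

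- A reader might infer that the 80% rule rests on a single late count. It does not: the same sentence names a tracker sheet, which may be a running log, although its format is not described. A cumulative threshold also needs no dated counts.
- A reader might infer that missing counts for people who withdraw would damage the analyses. They would rarely matter. The per-protocol set also needs 80% of 16 sessions (12.8, so 13), which most withdrawers would fail anyway. The primary analysis is worded for those who completed the trial, and its model does not use capsule intake.
- A reader might take 63% as the trial's real power. The article gives 2% as the difference to detect and does not say that it presumes perfect intake. The 80% is a minimum for each person, so a group in which everyone meets it will usually average more. Nothing shows how far interim checks would raise intake.

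There is also a worry about blinding. Containers are labelled A or B, so each label marks a whole arm, and more handling means more exposure to that code. The article does not say that the trainers are blinded. This bears on who should do the check, but it does not defeat it: the planned end-of-study count already involves the same capsules.

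**Conclusion.** The concern holds as a minor, cheaply corrected weakness in conduct. As stated, low intake of the randomised product is found only after dosing ends, with at least 96 of 112 capsules taken away from sessions, in a design that has 16 supervised sessions at which it could be found earlier. The main cost is possible dilution of the primary comparison; a lesser one is a per-protocol classification that is computable but harder to verify.

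The size cannot be fixed from the article. The illustrative fall from 82.0% power to 73.5% or 63.3% rests wholly on an effect proportional to intake and on assumed mean intakes of 90% and 80%. No stated figure is wrong, and no two sections conflict.

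**What to change.** In Supplements, provide for existing blinded staff who do not assess outcomes to count capsules and review the tracker at set training sessions, for example weekly or fortnightly. Each check should leave a dated entry, with a standard reminder, identical in both arms, when intake falls short. Keep the end-of-study count. In Statistical methods, state that the cumulative count, reconciled with the tracker, defines the 80%. Dose and dosing schedule are untouched.

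The cost is a few minutes per participant at sessions already held, and some data entry; no new visit or extra staff is needed. The downside is that the adherence observed becomes adherence under reminders, which the report should say. The article describes recruitment as still ongoing, so later participants could benefit. If dosing has already finished, the report should state that home intake was assessed only at the end.
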